## Methods

### Trial design

Multi-centered, parallel groups, controlled, triple blind, randomized clinical trial (RCT) subdivided in 2 strata as a function of the hemoglobin (Hb) levels at the start of the pregnancy:

– Stratum #1: If the levels of Hb are situated between 110 and 130 g/L, the individual will be randomly assigned to an iron dose supplement of 40 or 80 mg/d

– Stratum #2: If the levels of Hb are >130 g/L, the individual will be randomly assigned to an iron dose supplement of 40 or 20 mg/d

The overall design of the study is summarized in Figure 1. This trial has been registered with EU Clinical Trials Register, EUCTR-2012-005480-28.

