### Interventions

The clinical follow-up of the pregnancy in the PCC will be according to the program set by RHS. This includes a clinical visit at recruitment into the present study, a visit every trimester, and one at 40 days post-partum (Figure 1).

In the recruitment visit before week 12 of the pregnancy, the inclusion criteria will be assessed (except the Hb levels and the number of fetuses) as well as the exclusion criteria. Informed consent will be solicited. A clinical history will be recorded, as will a questionnaire regarding the ingestion of iron supplements, multi-vitamins, or other treatments (Drugs_Q) and, if a smoker, the Fagerstrom test for tobacco dependency. A blood sample for standard biochemical analyses (including hemoglobin) will be sent for processing in the centralized laboratory.

At visit 1, around the 12th week of gestation, Hb levels will be evaluated as will be the number of fetuses (using echography) to confirm that the inclusion criteria are fulfilled. If fulfilled, the individuals will be retained in the study and, if not, will be transferred out of the study, and considered a screening failure. The remaining women will be assigned to Stratum #1 or Stratum #2 of the study and will be randomized with respect to iron supplement prescription. Clinical history will be taken, including the use of multi-vitamins and iron supplements (on the questionnaire abbreviated as “Drugs_Q”) and the following questionnaires filled-in: Food Frequency Questionnaire (FFQ); International Physical Activity Questionnaire (IPAQ); State-Trait of Anxiety Inventory (STAI) and the Fagerstrom questionnaire (Fagerstrom_Q). The ultrasound data on the fetus will be recorded. Venous blood will be taken for analyses, the results of which will be reviewed in the next clinical visit. The iron supplementation that will be needed at the next visit will be prepared for distribution. Adverse events occurring since the previous visit will be recorded.

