### Outcomes

#### Primary outcomes

Principal variables in the pregnancy are iron status of the mother at each clinical visit (anemia, ferropenic anemia, risk of hemoconcentration) and birth weight of the baby.

Definition of main outcome variables

– Anemia is defined as Hb <110 g/L in the 1st and 3rd trimester, Hb <105 in 2nd trimester, Hb <120 g/L post-partum [21].

– Ferropenic anemia is defined as: Hb < the normal limit, and serum ferritin (SF) <15 μg/L [22].

– Hemoconcentration risk is defined as: Hb >130 g/L in the 2nd and 3rd trimester [4].

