#### Analysis of the primary outcome

The effects of iron dose supplement in each RCT on the biochemical iron status and mother-child health will be compared using regression models adjusted for those variables that can influence the relationship. Logistic regression or Cox models will be applied for qualitative variables such as, for example, the percentage of anemia or hemoconcentration at the end of pregnancy. Linear multiple regression models will be applied for dependent quantitative variables. The models will be adjusted for those variables that biologically affect the relationships studied, such as the serum ferritin levels, presence of alterations in the HFE gene, age of the mother, gestational age, parity, anthropometric indices, diet, and lifestyle, and the interactions between these variables. Initially included in the model will be all those variables that form part of the theoretical model and, in a second phase, the variables for entry into the model will be selected step by step (forward and backward) to achieve the most reduced stable models.

Conditions for the application of models will be verified using standard techniques that are based, essentially, on residuals analysis. The bilateral null hypothesis of normality, no difference, and non-significance of the regression coefficients, will be rejected when their probabilities are <5%. The data will be analyzed using the latest version of SPSS/PC package for Windows.

Data will be analyzed in 2 ways:

a) Intention-to-treat analysis

The principle of “intention-to-treat” is a way of analyzing the results that considers all individuals entered into the study, according to the group to which they were originally assigned, although they may not have complied with the protocol. In this case, in all the circumstances that have led to not having hemoglobin determinations before delivery, we will proceed to incorporate at this time-point the immediately-prior determination of hemoglobin. All randomized participants randomized who had received at least one dose of study medication will be included.

b) Per-protocol analysis

Included in the analysis will be only those pregnant women who received the allocated intervention at randomization. The per-protocol population (PP) will include those participants who had taken at least the 80% of the study medication, with proper assessment of adherence, or without any major protocol violations.

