Pregnant women diagnosed with anemia at the start will be treated according to the usual protocol, and not as a part of the current study. Women diagnosed with anemia posteriorly, will be treated with standard therapy, but will remain part of the study in the intention-to-treat analysis. However, they will not be considered in the per-protocol analysis.

Data missing from the study variables will be treated with the direct likelihood method [34] when no data is available. In these cases, the profile of pregnant women will be used to adjust the estimates of these parameters.

An analysis of sensitivity will be performed using a mixed model based on constraint-based patterns of missing values without dependence on the future to assess the robustness of the main results of the Mixed Model Repeated Measures against the possible transgression of random default assumption.

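### Carrying the last hemoglobin forward to the pre-delivery time-point makes early leavers reflect their enrolment stratum, which mainly distorts the Stratum 2 hemoconcentration comparison

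*Protocol article*

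**What the plan says.** The intention-to-treat paragraph under Analysis of the primary outcome covers every circumstance of "not having hemoglobin determinations before delivery, we will proceed to incorporate at this time-point the immediately-prior determination of hemoglobin". This is last observation carried forward for Hb at the end of pregnancy. The same section analyses qualitative outcomes, such as the percentage with anemia or hemoconcentration, by logistic or Cox regression.

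Trial design sets the strata. For Stratum 1 the condition is "If the levels of Hb are situated between 110 and 130 g/L"; for Stratum 2 it is "If the levels of Hb are >130 g/L".

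Primary outcomes sets the events: "Anemia is defined as Hb <110 g/L in the 1st and 3rd trimester, Hb <105 in 2nd trimester, Hb <120 g/L post-partum", and "Hemoconcentration risk is defined as: Hb >130 g/L in the 2nd and 3rd trimester".

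The end of the statistical section adds a second rule, "Data missing from the study variables will be treated with the direct likelihood method", and a sensitivity analysis meant to test "the main results of the Mixed Model Repeated Measures against the possible transgression of random default assumption".

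**The concern.** The cut-offs that admit women to a stratum are the same cut-offs that define the third-trimester events. If the only Hb available is at enrolment level, carrying it to the end of pregnancy returns the stratum label as the outcome. That value dates from about week 12, when supplementation starts, so it holds no information on dose.

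Two consequences follow. If such losses are equal in the two arms, a constant is mixed into both and the dose contrast shrinks. If they are unequal, the difference in losses appears as a difference in outcome. In Stratum 2 the arm that loses more women early looks worse; in Stratum 1 it looks better. The Discussion expects gastrointestinal effects to reduce adherence, and the arms differ in dose, so unequal loss is plausible, although the article does not quantify it.

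A smaller problem affects women who leave after week 24. Their second-trimester Hb is judged against third-trimester limits, so a value of 105 to below 110 g/L, which was not anemia when measured, becomes anemia when carried.

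**Working it through.** **Inputs (Sample size section).** Stratum 1 iron deficiency anemia 23.5%; Stratum 2 hemoconcentration risk 14.7%; a reduction of 10 points, hence 13.5% and 4.7%; one-sided alpha 0.05; beta 0.20; drop-out 35%; 283 and 156 women per arm. The statistical section tests two-sided at 5%.

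**Reproducing the plan's figures.** The arcsine formula n = 2(1.645 + 0.842)² / h², with h = 2·arcsin√p₁ − 2·arcsin√p₂, gives:
- Stratum 1: h = 0.2597, n = 183.3; 183.3/0.65 = 282.01, rounded up to 283.
- Stratum 2: h = 0.3499, n = 101.0; 101.0/0.65 = 155.4, rounded up to 156.

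Both match.

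**Threshold check.** An Hb in 110–130 is neither below 110 nor above 130, so if carried it is a non-event on both outcomes. An Hb above 130, if carried, is always hemoconcentration.

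**Effect on the rates.** Let f be the share of an arm whose only Hb is at enrolment level. The article does not give f. I take 5% to 35%, the upper end being the whole planned drop-out. Everyone else is assumed to show the planned rates.
- Stratum 1 observed rate = (1 − f)p
- Stratum 2 observed rate = f + (1 − f)p

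Power = Φ[(d − 1.96·SE₀)/SE₁], where d is the difference in rates, SE₀ = √(2p̄(1 − p̄)/n) and SE₁ = √([p₁(1 − p₁) + p₂(1 − p₂)]/n).

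Example, Stratum 2 at f = 15%: 0.15 + 0.85 × 0.147 = 0.275 and 0.15 + 0.85 × 0.047 = 0.190, so d = 0.085. SE₀ = 0.0478 and SE₁ = 0.0476. Power = Φ[(0.085 − 0.0937)/0.0476] = Φ(−0.18) = 43%.

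| f, Stratum 2, n = 156 per arm | Observed rates | Two-sided power |
|---|---|---|
| 5% | 19.0% vs 9.5% | 67% |
| 15% | 27.5% vs 19.0% | 43% |
| 35% | 44.6% vs 38.1% | 21% |

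**Comparators.** Analysing only the completers (156 × 0.65 ≈ 101 per arm) at the planned rates gives 67%. Leaving out just the f women, with no carried value, gives 83%, 79% and 67% at f = 5%, 15% and 35%. On the one-sided basis of the sample-size section, carry-forward at f = 35% gives 32%.

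**Stratum 1.** At f = 35%, 23.5% vs 13.5% becomes 15.3% vs 8.8%, with two-sided power 66% against 70% for the completers (283 × 0.65 ≈ 184 per arm).

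**No dose effect, unequal f.**
- Stratum 2, true rate 14.7% in both arms, f = 15% vs 25%: 27.5% vs 36.0%, a spurious 8.5 points; rejection about 37%.
- Stratum 2, f = 5% vs 10%: 19.0% vs 23.2%; rejection about 15%.
- Stratum 1, true rate 23.5% in both arms, f = 15% vs 25%: 20.0% vs 17.6%; rejection about 11%.

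**The case against.** A reader might infer that every Stratum 1 drop-out can never be an event and every Stratum 2 drop-out always is. The article does not support that, for three reasons.
- Blood is drawn at week 24, and a sample is requested at the discontinuation visit. Women with either value are not fixed by enrolment.
- Under Participant withdrawal, women diagnosed as anemic count as therapeutic failures in the intention-to-treat analysis. A Stratum 1 woman found anemic at week 24 who then leaves is therefore a failure.
- The stratum is set by the recruitment sample, but at visit 1 "Venous blood will be taken for analyses, the results of which will be reviewed in the next clinical visit". If that sample gives the last Hb, it may fall on the other side of a cut-off. It is still taken at about week 12 and so carries no dose effect, but the fixed score becomes essentially every woman rather than strictly every woman.

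These points stand and limit the claim to women with no Hb after about week 12. They lower f; they do not remove the mechanism.

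It is also fair to say that f = 35% is an extreme, that the false-positive rates rest on an assumed difference between arms, and that much of the Stratum 1 shortfall comes from drop-out and from a two-sided test on a one-sided sample size, not from carry-forward.

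A second tempting reading is that the two missing-data rules flatly contradict each other. Direct likelihood could be meant for cases with nothing to carry, and the mixed model could be detailed in a document not shown. Unreconciled is the accurate word: the article does not say which rule governs the end-of-pregnancy Hb, or how the mixed model relates to the logistic or Cox analysis.

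**Conclusion.** The point holds for the Hb-based primary outcomes, for women with no Hb after about week 12, and chiefly for hemoconcentration in Stratum 2. Birth weight, also primary, is unaffected.

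In Stratum 2, an early-loss share of only 5% already brings power down to that of a completers-only analysis after the full 35% drop-out, and larger shares do worse. The more serious risk is a false dose effect when early loss differs by arm: about 15% rejection for a 5-point difference and about 37% for a 10-point difference, against a nominal 5%. In Stratum 1 the dilution is small.

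The sizes rest on the assumed f and on all other women following the planned rates; the direction follows from the article's own cut-offs. This should be fixed before analysis. It does not show that the outcome of every drop-out is settled at enrolment.

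**What to change.** Delete the carry-forward sentence and name one missing-at-random method as primary for the Hb outcomes. Either of these would serve:
- the direct-likelihood repeated-measures model that the article already mentions, fitted to continuous Hb; or
- multiple imputation of week-36 Hb within stratum and arm, using all earlier Hb values, including discontinuation samples.

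Derive anemia and hemoconcentration from that method at the third-trimester limits, so that no week-12 or week-24 value stands in for week 36. Keep the therapeutic-failure rule for women diagnosed as anemic, and say how it enters the derivation. Restate the pattern-based sensitivity analysis as a variant of the same model.

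The cost is wording in the statistical section and some programming, with no extra data or participants.

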At visit 2, around week 24 of gestation, clinical history will be taken, and will include the Drugs_Q, which, from this visit onwards, includes the adherence to the iron supplementation prescribed. The following questionnaires are filled-in: FFQ; IPAQ; STAI, Fagerstrom_Q. The fetal ultrasound data will be registered. The biochemical analyses/results will be reviewed and a further blood sample taken for analysis, the results of which will be reviewed at the next clinical visit. The iron supplementation that will be needed at the next visit will be prepared for distribution. Adverse events occurring since the previous visit will be recorded.

At visit 3, around week 36 of gestation, the clinical history will be taken, the Drugs_Q as well as the FFQ; IPAQ; STAI, Fagerstrom_Q questionnaires will be filled-in. The fetal ultrasound data will be recorded and the biochemical results will be evaluated. A further blood sample will be taken for analyses, the results of which will be discussed at the next clinical visit.

The iron supplementation that will be needed at the next visit will be prepared for distribution. Adverse events occurring since the previous visit will be recorded.

At visit 4 (40 days post-partum), the clinical history will be taken, the Drugs_Q and the FFQ; IPAQ; STAI; Fagerstrom_Q questionnaires will be filled-in. A questionnaire on post-partum depression (Edinburgh Postnatal Depression Scale; EPDS) and the Parenting Stress Index (PSI) will be applied. The standard laboratory analyses results will be discussed. A further blood sample will be taken for analyses. Data on birth and the newborn will be recorded (weight and height). Clinical history of the baby will be recorded, including: anthropometric data (weight, height, head circumference) and cognitive development will be assessed (Bayley III), as well as behavioral and temperament (Early Infancy Temperament Questionnaire; EITQ). Adverse events occurring since the previous visit will be recorded.

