#### Iron supplementation

Starting from around the 12th week of gestation and continuing up to partum, adherence to prescription will be recorded. The dose assignments will be random and followed-up blind for each RCT stratum. The principal active ingredient is ferrimanitol ovoalbumin. The doses of 20 mg, 40 mg and 80 mg per day of elemental iron correspond to 150 mg, 300 mg and 600 mg ferrimanitol ovoalbumin. The reference dose is 40 mg/d, similar to that routinely prescribed in clinical practice [14].

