#### Discontinuation visit

This visit will take place only in case of the participant’s withdrawal from the study at any time outside the scheduled timetable. The exact date and reason for discontinuation will be registered. If possible, the healthcare professional will assess the woman’s health status via clinical history notes, and an ultrasound. A blood sample will be solicited for routine tests. The adherence to the iron supplementation up until the discontinuation of the treatment will be recorded, as will any adverse events. All the questionnaires will be filled-in, including: FFQ; IPAQ; STAI, Fagerstrom_Q. In case of having given birth, all the variables related to delivery and the newborn will be collected and a questionnaire on post-partum depression (Edinburgh Postnatal Depression Scale; EPDS) and the Parenting Stress Index (PSI) will be applied.

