### Sample size

The principal variables taken into account in calculating the size of sample needed are iron deficiency anemia, risk of hemoconcentration in the third trimester of pregnancy, and birth weight of the baby.

To achieve the study’s main objective, sample size is calculated in accordance with the following parameters: an alpha risk of 0.05 and a beta risk of 0.20 in a one-tailed test of comparison. A drop-out rate of 35% is factored-in.

To calculate the sample size needed to reduce the prevalence of iron deficiency anemia and hemocentration risk by 10 points, we consulted previous data from our research group [5,6,8]. We had observed a prevalence of 23.5% of iron deficiency anemia in the 3rd trimester in pregnant women with Hb levels of 110-130 g/L in the first trimester and a prevalence of risk of hemoconcentration of 14.7% in the 3rd trimester of pregnant women who started pregnancy with Hb levels of 130–150 g/L.

We found that, in Stratum #1 of the RCT, it will be necessary to include 283 women in each group and in Stratum #2 of the RCT 156 women would be necessary in each group.

With respect to child development, to detect differences in weight of the newborn ≥200 g taking into account a standard deviation (SD) of 450 g [5], the estimation suggests that it will be necessary to have 106 women in each group.

Hence, the overall study sample is calculated as 878 women: 566 in Stratum #1 and 312 in Stratum #2.

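### The intention-to-treat set is defined in two conflicting ways: all women as assigned, and only randomised women with at least one dose

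*Protocol article*

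**What the plan says.** Paragraph a) under Analysis of the primary outcome contains both rules. It first describes the intention-to-treat population as "all individuals entered into the study, according to the group to which they were originally assigned, although they may not have complied". It ends: "All randomized participants randomized who had received at least one dose of study medication will be included". Between the two, it says that a missing hemoglobin before delivery is replaced by the immediately preceding value.

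Four other places bear on who would have a dosing record:

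- Interventions, visit 2 (about week 24): the drug questionnaire is the one "which, from this visit onwards, includes the adherence to the iron supplementation prescribed".
- Iron supplementation: from about week 12 until delivery, "adherence to prescription will be recorded".
- Discontinuation visit: this applies to "withdrawal from the study at any time outside the scheduled timetable", and there: "The adherence to the iron supplementation up until the discontinuation of the treatment will be recorded, as will any adverse events".
- Discussion: the count of returned units comes from an adherence questionnaire applied at the clinical visits.

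Under Sample size, the allowance for loss is stated without a split by time or cause: "A drop-out rate of 35% is factored-in". The text after the per-protocol definition names direct likelihood for missing data.

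**The concern.** The two rules give different populations. A woman who is randomised and takes nothing belongs to the first and not to the second. If she still attends visits 2 to 4, she has a measured hemoglobin and a recorded birth weight, and the one-dose rule discards both.

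The usual defence of a one-dose rule is that, under blinding, failure to start cannot depend on the assigned arm. That defence needs the dosing status of every woman to be known. Here supplementation starts at about week 12, and the scheduled questionnaire first asks about adherence at about week 24. A woman who starts, tolerates the iron badly and disappears without a discontinuation visit may have no dosing record. If she were then treated as undosed, her exclusion would follow from something that happened after exposure. The arms in each stratum differ twofold in iron dose, and the Discussion names gastrointestinal effects as a threat to adherence, so such losses could differ by arm. Intention-to-treat is the only one of the two planned analyses that is meant to preserve the randomised comparison; the per-protocol set requires at least 80% of the medication.

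**Working it through.** **1. The plan's own sample size.** Inputs from Sample size: one-sided alpha 0.05, power 0.80, 23.5% to 13.5% (Stratum 1), 14.7% to 4.7% (Stratum 2), 35% drop-out. The arcsine formula is

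n = 2(z₀.₉₅ + z₀.₈₀)² / [2(asin√p₁ − asin√p₂)]², then n / (1 − 0.35).

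- Stratum 1: n = 184; 184 / 0.65 = 283.1 (stated 283).
- Stratum 2: n = 101; 101 / 0.65 = 155.4, rounded up to 156 (stated 156).

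The stated sizes reproduce, so this point disputes none of them.

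**2. How many women the one-dose rule could remove.** The document gives no share never dosed or without a dosing record. Assumed range: 2%, 5%, 10%. Of 878 women: 0.02 × 878 = 18; 0.05 × 878 = 44; 0.10 × 878 = 88.

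**3. Power cost.** With m women left per arm and no other loss, and p̄ the mean of p₁ and p₂,

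power = Φ{[0.10√m − 1.645√(2p̄(1 − p̄))] / √[p₁(1 − p₁) + p₂(1 − p₂)]}.

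| Share excluded | Stratum 1 (283 per arm) | Stratum 2 (156 per arm) |
|---|---|---|
| 0% | 0.924 | 0.913 |
| 2% | 0.919 | 0.908 |
| 5% | 0.912 | 0.900 |
| 10% | 0.898 | 0.886 |

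The largest fall is 2.7 percentage points, and all of it lies inside the 35% allowance.

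**4. Bias.** Take Stratum 1 with no true effect: 23.5% anemia in both arms, and an assumed 40% among excluded women. The rate left after excluding a share e is (0.235 − 0.40e) / (1 − e).

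- e = 5%: 0.215 / 0.95 = 22.6%
- e = 10%: 0.195 / 0.90 = 21.7%
- e = 15%: 0.175 / 0.85 = 20.6%

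Exclusion of 5% in both arms gives a spurious difference of 0.0 points; 5% against 10% gives 1.0 point; 5% against 15% gives 2.0 points. The planned effect is 10 points.

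**5. What carry-forward would do to the retained women.** A woman lost before visit 2 has only early-pregnancy hemoglobin. If the value carried is the one that placed her in her stratum, or stays on the same side of the cut-offs, she counts as non-anemic in Stratum 1 (110 to 130 g/L) and as at risk of hemoconcentration in Stratum 2 (above 130 g/L), whatever her arm. With a share L of such women in each arm, a true 10-point difference shrinks to 10(1 − L): 9.5 points at L = 5%, and 6.5 points if the whole 35% were lost this early. Removing the one-dose condition without settling the missing-data rule would therefore exchange one problem for another.

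**The case against.** A reader might infer that no dose is documented before visit 2, so that early drop-outs in general leave the primary analysis. The document does not support that, for these reasons:

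- A discontinuation visit with an adherence record is planned for off-schedule withdrawal, and this can fall before week 24. The Iron supplementation section also says that recording runs from about week 12.
- Nothing says that a missing adherence record counts as no dose. Proper assessment of adherence is asked for only in the per-protocol definition, and receipt of a dose could be read as dispensing.
- A woman who stops because of intolerance has taken at least one dose and meets the condition. A woman who never starts cannot have reacted to a dose, and the packs look alike.
- The article says that data are analysed in two ways and names neither as primary.
- Taking half of the 35% allowance as undocumented early loss (0.175 × 283 = 50 and 0.175 × 156 = 27 per arm) has no basis in the text. The 35% covers all loss over the whole study.

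All of this stands, and it limits the exposed group to women who never start and women lost silently before visit 2. It does not remove the contradiction. The returned-unit count does not close the gap either, because it is obtained at visits that a silently lost woman does not attend. Nor is the matter one of detail left to a fuller plan: both rules are stated, and they disagree.

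**Conclusion.** The point holds as a conflict within one paragraph: the stated principle includes all women as assigned, and the stated inclusion rule is a modified intention-to-treat set under the same label. Applied as written, the last sentence removes women who never start, and it may remove silent early losses if an absent record is taken as no dose.

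The consequences are small and conditional. Power falls by at most 2.7 points for exclusions of up to 10%, which is an assumed range. Bias is nil when exclusion is equal between arms and about 1 to 2 points under the assumed unequal patterns, which also take 40% anemia among excluded women; blinding makes such imbalance less likely but does not rule it out. The document gives no figure that would narrow these ranges. The correction is worth making because it is cheap and protects the randomised comparison, not because a large error has been shown.

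**What to change.** In paragraph a), delete the closing sentence with the one-dose condition and define the intention-to-treat set as all randomised women, analysed in their assigned arm. If a one-dose set is wanted, call it modified intention-to-treat or safety, report it as secondary, say what counts as having received a dose and how a missing record is classified, and give the number excluded by arm.

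In the same edit, state that missing outcomes of the retained women are handled by the direct likelihood method already named, and withdraw the carry-forward of early-pregnancy hemoglobin for them. Direct likelihood assumes that data are missing at random; the sensitivity analysis already planned on patterns of missing values is the place to test that.

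The cost is one sentence deleted and one or two rewritten. The required sample size, the visits and the data collection do not change.

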#### Participant withdrawal

Participants will be free to withdraw from the trial at any time, and without the need to provide any reason. The information that may already have been collected on participants will still be used. Withdrawal from the study will not affect the standard of care received from the practice. If participants withdraw before randomization, they will be replaced by an appropriate substitute.

The pregnancies diagnosed as anemic during the RCT will have the iron supplementation from the RCT changed, and will be treated according to the standard clinical practice protocol. These women will continue forming part of the study and will have the same follow-up, except they will be considered as therapeutic failures in the intent-to-treat statistical analyses, and will not be taken into account in the protocol analysis.

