### Participant timeline

Clinical follow-up of the pregnancy in the PCC will be according to the program set by ASSIR. The participant timeline is detailed in Figure 1

– Recruitment visit (previous to week 12 of gestation)

– 1st visit of the study (around 12th gestational week)

– 2nd visit of the study (around 24th gestational week)

– 3rd visit of the study (around 36th gestational week)

– 4th visit of the study (40 days post-partum)

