– Loss to follow-up. We hope to reduce this by taking advantage of the clinical visits that the pregnant women would normally have with her gynecologist/obstetrician. As such, she would not be required to undertake additional activities/visits by participating in the current trial. Further, we have increased the study sample size so as to compensate for possible loss to follow-up.

– The supplementation with iron can produce gastrointestinal side effects that can affect the adherence to treatment. To reduce this effect, the principal component of the supplement will be ferrimanitol ovalbumin which has been shown to have greater bioavailability and better tolerance than ferrous sulfate.

– It is difficult to know the adherence to the prophylactic iron supplement. To improve the registry, we will apply a semi-structured questionnaire on the degree of adherence to the prescription in all the clinical visits during pregnancy. This will indicate the number of units that have been returned to the investigator each week.

A primary strength of the study is its rigorous methodology that involves a large number of health-care professionals and patients, which will strengthen the validity of the findings. Conclusive outcomes would help the obstetrician in deciding the best iron supplementation pattern required to promote maternal and infant health. Initial hemoglobin levels that are routinely collected on all pregnant women attending the clinic, and there will not be any additional procedures that could dissuade participation by the pregnant woman.

Our findings would contribute to developing guidelines for good clinical practice.

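### The per-protocol definition joins its criteria with 'or', so it admits women with a major violation and, read plainly, women below 80% intake

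*Protocol article*

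**What the plan says.** Under *Analysis of the primary outcome*, item b), the protocol article builds the per-protocol population in two sentences. The first is a general restriction: "Included in the analysis will be only those pregnant women who received the allocated intervention at randomization". The second gives the working criteria, namely women who had "taken at least the 80% of the study medication, with proper assessment of adherence, or without any major protocol violations".

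One further exclusion applies. Women diagnosed with anemia after the start stay in the intention-to-treat analysis, but the *Statistical methods* section adds: "However, they will not be considered in the per-protocol analysis". *Participant withdrawal* says the same, that these women "will not be taken into account in the protocol analysis".

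The article does not define a major protocol violation. It does not say whether low intake counts as one, and it does not restate the criteria elsewhere.

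**The concern.** A per-protocol set should hold women who took the assigned dose, whose intake is known and who followed the protocol in its essentials. These are cumulative requirements. Joined by *or*, they become alternatives, and failing one can be offset by meeting another.

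This matters because the trial compares doses: 40 against 80 mg/d in Stratum #1, and 40 against 20 mg/d in Stratum #2. The *Discussion* itself names gastrointestinal side effects as a threat to adherence. The per-protocol analysis is the one of the two that should show the contrast in women who took what they were assigned. If women with low intake or major violations remain, the contrast can be blurred, and agreement with the intention-to-treat result then says less than it appears to. Wording open to two readings also leaves the choice of set to be made after adherence is known.

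**Working it through.** There is no stated figure to reproduce; the check is one of logic. Let I = at least 80% of the medication taken, P = adherence properly assessed, N = no major protocol violation. The sentence can be parsed in two ways:

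- Plain reading: (I and P) or N.
- Narrow reading: I and (P or N), with the two closing phrases taken as parallel qualifiers of the 80% intake.

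The joint rule is I and P and N.

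| I | P | N | Plain | Narrow | Joint |
|---|---|---|---|---|---|
| yes | yes | yes | in | in | in |
| yes | yes | no | in | in | out |
| yes | no | yes | in | in | out |
| yes | no | no | out | out | out |
| no | yes | yes | in | out | out |
| no | yes | no | out | out | out |
| no | no | yes | in | out | out |
| no | no | no | out | out | out |

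The plain reading admits five combinations, the narrow reading three and the joint rule one. Two wrongly admitted groups are common to both readings: women with a major violation whose intake was sufficient and assessed, and women whose 80% intake was not properly assessed. The plain reading adds women below 80% intake who have no major violation. A woman who is below 80% and also has a major violation is out on either reading.

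Next, whether other text closes the gap:

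- The first sentence of item b) asks that the allocated intervention was received. It sets no level of intake and does not mention violations. The intention-to-treat set already requires at least one dose, so this sentence need not remove many more women.
- The anemia exclusion removes women by diagnosis, not by intake, assessment or violation.

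Neither makes the criteria joint.

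For scale only, on assumed rates (the document gives none): let a = share with at least 80% intake, b = share without a major violation, independent of each other, adherence assessed in every woman, before the anemia exclusion. The planned total is as stated: "the overall study sample is calculated as 878 women: 566 in Stratum #1 and 312 in Stratum #2".

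- Joint rule: a × b. Plain reading: 1 − (1 − a)(1 − b).
- At a = 0.80, b = 0.90: joint 0.72 (632 of 878); plain 1 − 0.20 × 0.10 = 0.98 (860 of 878). Share of the plain set failing a criterion: (0.98 − 0.72)/0.98 = 27%.
- Over a = 0.60 to 0.90 and b = 0.80 to 0.95: joint 48% to 86%, plain 92% to 99.5%, share failing a criterion 14% to 48%.
- Narrow reading: the set is a, and the share with a major violation is 1 − b, so 10% at b = 0.90 and 5% to 20% over the range.

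These figures show how the rules differ. They do not predict this trial.

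**The case against.** The strongest defence is that the *or* is a drafting slip. The first sentence of item b) is restrictive in tone, the article has other slips of language, and on the narrow parsing a woman with, say, 30% intake never qualifies. Much of this stands. The sentence is ambiguous rather than plainly reversed, and the intent was probably cumulative. But no text corrects it, and even the narrow parsing lets in women with a major violation.

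A second defence is that a fuller protocol or analysis plan may define a major violation so as to include intake below 80%. That would remove the low-intake group, but women with another major violation and adequate, assessed intake would still enter. Nor is this a detail left to another document: the article states the rule, with its threshold.

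Two stronger inferences are tempting and do not hold.

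- A reader might infer that the per-protocol set becomes nearly the whole randomised set. The anemia exclusion rules that out as a general statement. *Sample size* cites 23.5% third-trimester iron deficiency anemia for the hemoglobin range of Stratum #1, and 23.5 − 10 = 13.5% if the targeted reduction is met. At those rates, even a rule that admitted everyone else would leave 100 − 23.5 = 76.5% to 100 − 13.5 = 86.5% of that stratum.
- A reader might infer that the adherence measure cannot support the 80% threshold, because the *Discussion* says of the questionnaire "This will indicate the number of units that have been returned to the investigator each week" while visits are about 12 weeks apart in pregnancy. But it also says "we will apply a semi-structured questionnaire on the degree of adherence to the prescription in all the clinical visits during pregnancy", and a form completed at a visit can record counts by week. The article does not describe packaging or returns, so no contradiction is shown.

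**Conclusion.** The definition is wrong as written. On either reading it admits women whom a per-protocol set should exclude: at the least, women with a major violation and women without a proper adherence assessment; on the plain reading, also women below 80% intake. This conclusion rests on the wording alone and needs no assumed rates.

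The consequence is limited to the per-protocol analysis, whose dose contrast can be blurred. The intention-to-treat analysis is unaffected, and nothing in the article rests the trial's conclusion on the per-protocol result. The size of the effect cannot be derived from the document; the shares in the illustration depend wholly on assumed rates and on independence. The correction is small, but it belongs in the plan before unblinding because the rule governs one of the two named analyses of the primary outcome.

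**What to change.** Restate item b) so that the per-protocol population must meet all of the following: at least 80% of the study medication taken, AND proper assessment of adherence, AND no major protocol violation. Keep the existing exclusion of women who become anemic as an additional condition, and say explicitly that the conditions are cumulative. Any analysis plan should carry the same wording.

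The cost is a change of wording in one sentence and a smaller per-protocol set, with wider confidence intervals. The intention-to-treat set does not change.
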